#### Ultrasound examination

At 6 and 24 months ultrasound imaging will be performed to examine the midline for any asymptomatic clinically not detectable incisional hernias. This will provide valuable information about the onset of an incisional hernia. Size and location of all incisional hernias noted radiographically will be registered, as well as complaints presented by the patients. Endpoint of this study will be at 2 years follow up. At this follow-up the presence of a hernia will be investigated by physical examination and ultrasound imaging.

#### Outpatient follow-up

The follow-up schedule is displayed in Table 3. During visits the following information will be gathered.

•Outpatient clinic visit at 1, 3, 12 and 24 months

○ Incisional hernia

○ Wound infection

○ Seroma formation

○ Other wound problems

○ Inguinal hernia

•Ultrasound at 6 and 24 months

•VAS score at 1 month

•VAS scores and Quality of Life forms preoperatively ( day of operation or the day before) and at 3, 12 and 24 months

**Table 3 T3:** Follow up schedule

**Evaluation moments**	**MOS SF-36 (1)**	**EQ-5D (2)**	**VAS score (3)**	**Outpatient clinic**	**Ultrasound**
Pre-operative	X	X		X	
1 month			X	X	
3 months	X	X	X	X	X at 6 months
12 months	X	X	X	X	
24 months	X	X	X	X	X

(1) MOS SF-36: Questionnaire concerning quality of life (SF-36 ™ Health Survey, Medical outcomes Trust, Boston, Massachusetts 02116, USA).

(2) EQ-5D: Euro Qol Group quality of life questionnaire.

(3) VAS score: Pain measurement tool on which patients can define their pain on a sliding scale.

### Economical evaluation

Cost effectiveness will be calculated after 2 years. The direct costs, admissions, operation costs, costs of materials and treatment of complications and incisional hernias, will be calculated. Quality Adjusted Life Years will be calculated.

An incisional hernia correction costs Є3777,-. When 100 patients are operated with the aid of a mesh insertion we estimate to prevent 15 incisional hernias (=Є56.655,-). One hundred meshes cost approximately Є30.000,-. We would save Є26.655,- if all incisional hernias are repaired. We did not include all extra costs as for example visits to the general practitioner, but these will be included in our final analysis.

### Statistical analysis

Three comparisons will be made leading to pair-wise comparison at alpha = 0.017 (=0.05/3) according to Bonferroni’s correction for multiple testing. Assuming a 30% rate of incisional hernia in group A, and about 10% in both groups B and C, for a power of 90% comparing group A versus group B and C, 92 patients are required in group A and 164 in groups B and C. Allowing for some dropouts, 100 will be included in the control group and 180 in each experimental group.

It is expected that differences between groups B and C can only be demonstrated with a very large number. Therefore it was decided to set the objective to showing “non inferiority” for onlay (group C) versus sublay (group B). Setting the non-inferiority margin at 10%, the power to show non-inferiority regarding the incidence rate of incisional hernia will be greater than 80%.

For the comparison of both experimental groups with the control group, Kaplan-Meier curves will be constructed and the log-rank tests will be performed. These logrank tests will be done with stratification by center and operation indication.

For the comparison of both experimental groups B and C, the cumulative 2-years probability will be calculated with the one-sided 98.3% confidence interval for the difference. Analysis will be done according to the intention-to-treat principle in comparing group A with groups B and C. For the comparison of groups B and C a per-protocol analysis will be the primary analysis.

Comparison of VAS and QOL scales between groups will be done using Repeated Measures Anova (SAS PROC MIXED) with baseline value, age, gender, operation indication and center as covariates.

The following putative risk factors regarding incisional hernia (smoking, infection, diabetes, corticosteroids) will be evaluated using Cox-regression.

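### Bonferroni at 0.05/3 for all three comparisons is valid but gives away power; Holm's procedure, with the non-inferiority test capped at one-sided 0.025, does better at the same 5% familywise error

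*Protocol article*

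**What the plan says.** All the relevant text is in the Statistical analysis section of the protocol article.

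- Multiplicity: Bonferroni over three tests, giving a "pair-wise comparison at alpha = 0.017 (=0.05/3") for each of them.
- Planning rates: "Assuming a 30% rate of incisional hernia in group A, and about 10% in both groups B and C".
- Superiority: "for a power of 90% comparing group A versus group B and C, 92 patients are required in group A and 164 in groups B" (the last figure covers the sublay and onlay groups alike). The planned enrolment is then 100 in the control group and 180 in each mesh group.
- Mesh against mesh: "Setting the non-inferiority margin at 10%, the power to show non-inferiority regarding the incidence rate of incisional hernia will be greater than 80"%.
- The Bonferroni level is carried into that comparison: "the cumulative 2-years probability will be calculated with the one-sided 98.3% confidence interval for the difference".

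The two comparisons with suture closure use stratified log-rank tests by intention to treat; their sidedness is not stated. The mesh comparison is per protocol. No step-down, hierarchical or gatekeeping rule is mentioned, so the single-step 0.05/3 is a stated choice.

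**The concern.** Single-step Bonferroni holds every test at 0.05/3 even after another null hypothesis has been rejected. Holm's procedure compares the smallest p-value with 0.05/3, the next with 0.05/2 and the last with 0.05, and stops at the first failure. It controls the familywise error at 5% under any dependence, which matters here because every pair of tests shares an arm. It also rejects everything Bonferroni rejects.

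What is at stake is the chance that the trial answers all three of its questions. The mesh comparison has the least reserve. Its power is above the stated 80% by little, and its primary analysis is per protocol, so exclusions reduce its sample directly. The superiority tests also gain, which would matter if the effect is smaller than planned. The Economical evaluation section expects mesh to prevent 15 hernias per 100 patients, whereas the sample size rests on a difference of 20 points.

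**Working it through.** **Inputs.** From Statistical analysis: rates 30/10/10%; 92/164/164 required and 100/180/180 enrolled (164 is read as per mesh arm, since 180 per arm follows); margin 10 points; per-test level 0.05/3; non-inferiority one-sided. Assumption: the log-rank tests are two-sided.

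**1. The plan's own figures.** Non-inferiority power is Φ(0.10/√(2 × 0.1 × 0.9/n) − z), with z = 2.128 for one-sided 0.05/3.

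- n = 164: SE = √(0.18/164) = 0.0331; 0.10/SE = 3.018; Φ(3.018 − 2.128) = 81.3%.
- n = 180: SE = 0.0316; Φ(3.162 − 2.128) = 85.0%.
- 80% power needs 159 per arm, so the stated figure of more than 80% holds. Losing more than 180 − 159 = 21 patients per arm (12%) to per-protocol exclusion would undo it.

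Superiority at 92/164, unpooled: SE = √(0.3 × 0.7/92 + 0.1 × 0.9/164) = 0.0532; Φ(0.20/0.0532 − 2.394) = 91.4%. The stated 90% is met.

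**2. What the cap does.** The levels for the last two Holm steps are 0.025 and 0.05. A non-inferiority p-value above 0.025 can therefore pass only at the last step, and capping it there at 0.025 changes no other decision. It follows that non-inferiority is concluded if its p-value is at most 0.05/3, or if it is at most 0.025 and at least one log-rank p-value is at most 0.05/3. In closed form, one-sided 0.025 gives 85.5% at n = 164 (+4.2 points) and 88.5% at n = 180 (+3.6 points).

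**3. Joint simulation.** Binomial arms shared across the three tests; two-sided pooled z-tests stand in for the log-rank tests; unpooled z-test for non-inferiority. Rates 30/10/10%, 92/164/164:

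| | Bonferroni | Holm, capped at 0.025 | Holm, uncapped |
|---|---|---|---|
| Non-inferiority | 81.7% | 85.4% | 90.7% |
| Each superiority test | about 95% | about 97% | about 97% |
| All three succeed | 75.8% | 82.8% | 88.1% |

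At 100/180/180, non-inferiority goes from about 85% to 89% with the cap.

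**4. Smaller effects.**

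- Suture rate 25%, mesh 10% (the 15-point effect of the Economical evaluation), 92/164/164: each superiority test goes from about 78% to 84–85%, and all-three success from 58% to 71% with the cap.
- Suture rate 20%, mesh 10%: the capped non-inferiority gain shrinks to about 2 points (81.7% to 83.8% at 164 per arm; 84.8% to 87.3% at 180).

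**5. Error control.** At 100/180/180, simulated familywise error under uncapped Holm was 3.7% to 3.9% in four null configurations; the cap can only lower it. With the mesh difference exactly at the margin and both superiority effects real (40/20/10%), false non-inferiority claims were 1.8% under Bonferroni, 2.7% with capped Holm and 5.2% with uncapped Holm. The small excesses over 1.67%, 2.5% and 5% come from the normal approximation.

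**The case against.** The strongest reply is that nothing is wrong. Bonferroni is valid, the trial was sized at 0.05/3, and it meets its stated 90% and more than 80%. This stands, and it limits the point to efficiency. A reader might infer that the trial is underpowered or that its type I error is not controlled; the document's own figures show neither.

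A reader might also take the gain for non-inferiority to be about 9 points (81.7% to 90.7%). That needs the mesh comparison to be tested at one-sided 0.05, three times the planned level, and raises false claims at the margin from 1.8% to 5.2%. With the cap the gain is 3.6 points in the same simulation. Nor is it right to say that the stricter level serves no error-control purpose: it does protect this particular claim, and even capped Holm gives up some of that protection.

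The last objection concerns the interval. Under Bonferroni, the decision and the fixed one-sided 98.3% bound always agree. Under Holm the level of the bound depends on the step reached, and the two reported bounds can fall on opposite sides of the 10% margin. This cost is real but small: under the cap the deciding level can only be 98.3% or 97.5%, and stating in advance which result governs removes the ambiguity.

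**Conclusion.** The point holds as a cheap improvement. Its direction is certain, because Holm controls the same 5% under any dependence and never loses a Bonferroni rejection. Under the planning rates at 92/164/164 the capped version adds about 4 points for non-inferiority, about 2 points for each superiority test and 7 points for success on all three (82.8 − 75.8). If the suture rate is 25%, the all-three gain is 13 points (71 − 58).

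These sizes rest on two-sided log-rank tests, on z-tests standing in for them, on equal 10% rates in the mesh arms, and on 164 being per arm. The gain for non-inferiority needs at least one superiority test to succeed. The section labels onlay as C and sublay as B, the reverse of the Intervention section; with equal rates this does not affect the figures.

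**What to change.** Before unblinding, replace the Bonferroni sentence with wording to this effect:

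> The two-sided log-rank p-values for suture against onlay mesh and suture against sublay mesh, and the one-sided non-inferiority p-value for onlay against sublay mesh, are tested by Holm's procedure at a familywise error of 5%. The non-inferiority test is never carried out above one-sided 0.025. The Holm decision governs. The confidence bound for the mesh comparison is reported at the level reached and, beside it, at 98.3%.

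The sponsor should confirm that the log-rank tests are two-sided. Naming the arms by technique avoids the reversed labels.

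The cost is a change of wording, with no patients and no new data. The price in inference is a bound whose level depends on the step reached, and a chance of a false non-inferiority claim at the margin of about 2.7% instead of 1.8%, still inside the 5% familywise limit.

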### Intervention

Patients will be randomized for three different closing techniques (1A: primary suture closure of the midline fascia, 2B onlay mesh supported closure and 3C sublay mesh supported closure). Both mesh techniques are extensively used in incisional hernia surgery. However, a powered randomized comparison of these two techniques has not been performed. Infection rates in these trials seem low, even in the presence of open bowel [36-41]. Because the study population will not be operated for an incisional hernia, which necessitates extended dissection of the abdominal wall in a previously operated area, infection rates are expected to be lower than the rates mentioned in the literature. Intra-peritoneal placement has not been considered given the high risk for adhesions between viscera and mesh [42].

The mesh will be fixed to the fascia structures with fibrin sealant (Tissucol DUO 500 2,0 ml (Baxter Deutschland GmbH, Unterschließheim, Germany) in order to avoid sutures subcutaneously, to prevent the production of seroma and to simplify the procedure [43]. Nowadays fibrin sealants are occasionally used in inguinal hernia surgery [44-46]. The mesh will be fixed adequately with fibrin sealant to the ventral part of linea alba and posterior rectus sheath. The Optilene Mesh LP, 6 × 35 cm, B. Braun Aesculap AG, Tuttlingen, Germany, will be used as it was shown to have an optimal fixation with fibrin sealant and to provide good tensile strength [47].

Only the first operations of each center will be supervised by one of the PRIMA trial research fellows. If during operation an incisional hernia was discovered the patient was excluded from the trial, as the interest of this study was incisional hernia prevention, not repair. All centers were familiar with the 4:1 suture length to wound length ratio concept although not measured. As the focus of the trial was on the effect of primary mesh augmentation versus common day practice closure, no measurements of the suture closure were done.

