### Mesh supported closure

#### Group B. Onlay mesh supported closure

First, the midline will be closed as indicated in group A.

The Optilene Mesh LP will be positioned on the primary closed midline fascia with an overlap of 3 cm at each side. The mesh will then be fixed with fibrin sealant (5 ml). The fibrin sealent will be applied on the entire surface of the mesh, and in one shot having permanent contact between the mesh and the tip of the joining piece. Immediately after application of the fibrin sealant, the mesh will be smoothed with the back of a forceps to get a good fixation of the mesh on the entire surface and especially on the suture line. If present, it is also possible to use spray fixation using the EASYSPRAY system, *Deutschland GmbH, Unterschließheim, Germany.* When laparotomy is larger then 25 cm use 2 applicators of Tissucol (10 ml). Subcutaneous tissue and skin are closed in a fashion preferred by the surgeon.

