#### Group C. Sublay mesh supported closure

A space will be created between both posterior rectus sheaths and the rectus muscle. Both posterior rectus sheath edges are sutured using a running slowly absorbable suture,*(Monoplus, USP1, Needle HRT48, 150 cm, B. Braun Aesculap AG, Tuttlingen, Germany)*. A suture length to wound length ratio of 4:1 was recommended (not measured). The Optilene Mesh LP will then be placed between the posterior rectus sheath and the rectus muscle with an overlap of 3 cm at each side and fixed with fibrin sealant (5 ml). The fibrin sealent will be applied on the entire surface of the mesh, in one shot having permanent contact between the mesh and the tip of the joining piece. Immediately after application of the fibrin sealant, the mesh will be smoothed with the back of a forceps to get a good fixation of the mesh on the entire surface and especially on the suture line. If present, it is also possible to use spray fixation using the EASYSPRAY system, *Deutschland GmbH, Unterschließheim, Germany.* When laparotomy is >25 cm use 2 applicators of Tissucol (10 ml). The midline anterior rectus sheath will be closed using a running slowly absorbable suture *(Monoplus, USP1, Needle HRT48, 150 cm, B. Braun Aesculap AG, Tuttlingen, Germany)*, covering the mesh. A suture length to wound length ratio of 4:1 was recommended (not measured). Subcutaneous tissue and skin will be closed in a fashion preferred by the surgeon.

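### The non-inferiority objective swaps the arm letters, so names and letters point a one-sided test in opposite directions

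*Protocol article*

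**What the plan says.** Three places in the Methods define the mesh arms in the same way. The Intervention section lists "2B onlay mesh supported closure and 3C sublay mesh supported closure", and the two arm headings read "Group B. Onlay mesh supported closure" and "Group C. Sublay mesh supported closure".

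The Statistical analysis section states the non-inferiority objective "for onlay (group C) versus sublay (group B"), with both letters reversed. It adds "Setting the non-inferiority margin at 10" percent, and claims that "the power to show non-inferiority regarding the incidence rate of incisional hernia will be greater than 80" percent. Each of the three comparisons is a "pair-wise comparison at alpha = 0.017 (=0.05/3").

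For the two mesh arms, "the cumulative 2-years probability will be calculated with the one-sided 98.3% confidence interval for the difference". That sentence, and the later one that makes the per-protocol analysis primary for this comparison, identify the arms by letter only. Neither says which arm is subtracted from which, or whether the limit is an upper or a lower one.

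**The concern.** In a two-sided comparison, exchanged labels would change only the sign of the estimate. Here the direction is the hypothesis: one arm is the test arm, the other is the reference, and a single limit is compared with the margin. The technique names make onlay the test arm. The letters, read with the arm definitions, make sublay the test arm. Both cannot be meant, and this sentence is the only place where the article states the hypothesis.

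At stake is what the onlay/sublay comparison may conclude. If the analysis were programmed from the letters and then reported by technique name, onlay could be declared non-inferior on a test that never put a limit on how much worse onlay is.

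**Working it through.** **Inputs, all from the Statistical analysis section.** Margin 10 percentage points, read as absolute because the interval is for a difference; one-sided alpha 0.05/3 = 0.0167, so z = 2.128; planned hernia rate about 10% in each mesh arm; 164 per mesh arm required (read as per arm) and 180 per mesh arm to be included.

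**Two readings of the one sentence.**

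- By name: non-inferiority if the upper limit of onlay − sublay (B − C under the arm definitions) is below 0.10.
- By letter: non-inferiority if the upper limit of C − B, that is sublay − onlay, is below 0.10.

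**Formula.** Normal approximation with unpooled variance:

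Pass probability = Φ( [0.10 − (p_test − p_ref)] / SE − 2.128 ), with SE = √[ p_test(1 − p_test)/n + p_ref(1 − p_ref)/n ].

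**The plan's own figure.** At 10% in both arms the difference is 0, so both readings give the same value.

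- n = 164: SE = √(0.18/164) = 0.0331; 0.10/0.0331 = 3.019; Φ(3.019 − 2.128) = 81.3%.
- n = 180: SE = √(0.18/180) = 0.0316; 0.10/0.0316 = 3.162; Φ(3.162 − 2.128) = 85.0%.

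The stated power above 80% therefore reproduces. Because it is the same in both directions, checking the power cannot reveal the swap.

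**Unequal rates.** The article gives no planning assumption under which the mesh arms differ, so the unequal rates below are illustrative. Worked example with n = 180, onlay 15%, sublay 10%: SE = √[(0.1275 + 0.09)/180] = 0.0348.

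- By name: (0.10 − 0.05)/0.0348 − 2.128 = −0.690, giving 24.5%.
- By letter: (0.10 + 0.05)/0.0348 − 2.128 = 2.187, giving 98.6%.

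| Onlay / sublay | By name | By letter |
|---|---|---|
| 10% / 10% (planned) | 85.0% | 85.0% |
| 8% / 10% | 96.8% | 70.0% |
| 12% / 10% | 61.8% | 93.5% |
| 15% / 10% | 24.5% | 98.6% |
| 20% / 10% (at the margin) | 1.7% | 99.9% |
| 10% / 15% | 98.6% | 24.5% |
| 10% / 20% | 99.9% | 1.7% |

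A simulation of 400,000 trials with Wald limits agrees: 84.9% in both directions at 10%/10%, 25.3% against 98.6% at 15%/10%, and 1.8% against 99.9% or more at 20%/10%.

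**The case against.** The best defence is that this is a labelling slip. The sentence names the techniques, and the names alone give a direction: onlay is judged against sublay. A program keyed to technique would be correct. A false claim about onlay needs an analyst to code by letter, trust the letters in this one sentence over three consistent definitions elsewhere, and still report by name. The comparisons of the mesh arms with suture closure, which carry the main objective, do not depend on the swap. Nor do the sample size and the power.

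All of that stands, and it limits the point. It does not remove it, because the sentences that specify the interval and the analysis set use letters only and offer no order of subtraction that would settle the matter.

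A reader might infer two stronger things. The first is that a test coded by letter would nearly always pass. The plan's figures do not support this: at 10% in both arms it passes exactly as often as the test by name, and it passes less often if sublay is the worse arm. Near-certain passing needs onlay to be truly worse by about 5 points or more, which the article nowhere assumes. The second is that the analysis is bound to go wrong because the randomisation system and database hold group letters. The section on registration and randomisation does not say how arms are stored. The Intervention section labels the arms with letters and technique names together. Coding by letter is a plausible risk, not a documented fact.

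**Conclusion.** The contradiction is certain: both letters in the non-inferiority objective are the reverse of the arm definitions. As written, the direction of a one-sided decision rule is ambiguous.

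The size depends on the true rates. Nothing changes at the planned rates. With a true difference of 5 points and 180 per arm, the two readings pass in 24.5% and 98.6% of trials, in an order set by which arm is worse. With onlay worse by exactly the margin, a test meant to pass in 1.7% of trials would pass in 99.9% if run by letter, and that would be an error if reported as a finding about onlay.

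These figures assume an absolute margin, 164 or 180 analysable patients per arm, simple proportions in place of Kaplan-Meier estimates, and unequal rates chosen for illustration. The harm further depends on the analysis following the letters and not the names. Whether it does cannot be told from the article. The point is confined to the onlay/sublay comparison, but there it determines what may be concluded, so it should be settled before that analysis is run.

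**What to change.** 1. Have the sponsor confirm which arm is the test arm. The names suggest onlay, but this should be confirmed, not presumed.
2. If the names are what was meant, correct the sentence to onlay (group B) versus sublay (group C).
3. State the rule so that it cannot be read two ways. H0: p_onlay − p_sublay ≥ 0.10; conclude non-inferiority if the upper one-sided 98.3% limit of onlay minus sublay is below 0.10.
4. Check that the analysis code, and the statistical analysis plan if there is one, use the same direction and identify arms by technique as well as letter.

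The cost is one corrected sentence, one added line and a short check of the code. Sample size, stated power, patients and data are unaffected.

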### Registration and randomization procedure

Patients who are scheduled for operation and who have given informed consent will be registered by contacting the trial coordinator using the telephone or using the online inclusion randomization system. Included patient are registrated in an online data base (designed and managed by HOVON data center, Rotterdam, the Netherlands) called TOP (Trial Online Process; see http://www.primatrial.nl). The patient name code, date of birth, name of caller, name of responsible physician, sex and eligible criteria will be registered. Every participating institution has its own login code.

Randomisation will take place at the end of the scheduled operation before closing the abdomen in the operating room by contacting the trial coordinator using the telephone or using the online inclusion randomization system. The patient will stay in the randomization group on an intention to treat principle.

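### Onlay versus sublay: non-inferiority can be claimed on the per-protocol set with no requirement that the intention-to-treat comparison agrees

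*Protocol article*

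**What the plan says.** The Statistical analysis section of the protocol article assigns analysis sets by comparison. Intention-to-treat is named for group A against groups B and C. For the two mesh groups it says: "For the comparison of groups B and C a per-protocol analysis will be the primary analysis". The decision tool is set out as "the cumulative 2-years probability will be calculated with the one-sided 98.3% confidence interval for the difference". The margin is given by "Setting the non-inferiority margin at 10" per cent, and the section adds that "the power to show non-inferiority regarding the incidence rate of incisional hernia will be greater than 80" per cent.

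No intention-to-treat analysis is named for onlay versus sublay, and nothing says what follows if the two sets disagree.

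Two statements elsewhere bear on this. The Registration and randomization procedure section has a general rule: "The patient will stay in the randomization group on an intention to treat principle". The Ethics section says that data of patients who withdraw will be evaluated in the final analysis. Neither makes intention-to-treat part of the non-inferiority decision.

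The group letters also conflict. The Intervention section and the group descriptions call onlay B and sublay C. The non-inferiority paragraph of the Statistical analysis section calls onlay C and sublay B.

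**The concern.** A per-protocol set is formed after randomisation, so the two arms within it are no longer protected against selection. Patients are randomised at the end of the operation, just before closure. Any failure to deliver the allocated closure, and any later event used to remove a patient, therefore happens after allocation.

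The two techniques differ in what they ask of the surgeon. Sublay needs a space to be created between the posterior rectus sheaths and the muscle, with both layers sutured. Onlay is laid on a midline already closed. Unequal non-delivery is plausible, although the article gives no rate for either arm. If patients whose mesh became infected, was removed or led to re-operation were left out, failures of the technique under test could leave the comparison with them. The resulting bias could favour either technique.

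At stake is a claim that onlay is no worse than sublay, made while the randomised comparison fails the same criterion. The Discussion bases the trial's high level of evidence partly on its being randomised, and this comparison would give up some of that protection.

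**Working it through.** **Inputs, all from the Statistical analysis section**
- Hernia rate of 10% in both mesh groups: "Assuming a 30% rate of incisional hernia in group A, and about 10% in both groups B and C".
- Margin of 10 percentage points.
- One-sided alpha 0.05/3 = 0.0167, from "pair-wise comparison at alpha = 0.017 (=0.05/3") and the one-sided 98.3% interval. The normal quantile is 2.128.
- Numbers per mesh arm: 164 required and 180 enrolled, from "Allowing for some dropouts, 100 will be included in the control group and 180 in each experimental group".

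**1. The plan's own power figure**

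Under the normal approximation with n per arm:

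SE = sqrt(2 × 0.1 × 0.9 / n) = sqrt(0.18/n); power = Φ(0.10/SE − 2.128).

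- n = 180: SE = 0.03162; 3.162 − 2.128 = 1.034; power 84.9%.
- n = 164: SE = 0.03313; 3.018 − 2.128 = 0.890; power 81.3%.
- n = 159: SE = 0.03365; 2.972 − 2.128 = 0.844; power 80.1%.
- n = 158: power 79.8%.

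The stated power of more than 80% is reproduced at both 180 and 164 per arm.

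**2. Can the two sets disagree?**

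The counts here are assumed, for illustration only. Take 18/180 hernias with sublay and 24/180 with onlay. Upper limit = difference + 2.128 × SE, with SE from the observed proportions.

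- Intention-to-treat: 13.3% − 10.0% = 3.3 points; SE = sqrt(0.1333 × 0.8667/180 + 0.1 × 0.9/180) = 0.0338; upper limit 3.3 + 2.128 × 3.38 = 10.5 points. Non-inferiority is not shown.
- Per-protocol, leaving out six onlay patients who all had a hernia: 18/174 − 18/180 = 10.3% − 10.0% = 0.3 points; SE = 0.0321; upper limit 0.3 + 2.128 × 3.21 = 7.2 points. Non-inferiority is shown.
- Leaving out only three such patients: 21/177 − 18/180 = 1.9 points; SE = 0.0330; upper limit 8.9 points. Non-inferiority is again shown.

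Six patients are 3.3% of one arm (6/180). As written, the plan would declare non-inferiority in the second and third cases.

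**3. Power if both sets must pass**

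Assume 180 randomised per arm, a per-protocol set of n per arm nested within them, and 10% hernia in both arms. The two test statistics are then approximately bivariate normal with correlation sqrt(n/180).

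- n = 159: correlation 0.940; joint power 78.4%.
- n = 164: correlation 0.955; joint power 79.8%.
- n = 165: correlation 0.957; joint power 80.05%.

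About 165 per-protocol patients per arm are needed for 80% joint power. That allows 180 − 165 = 15 per arm (8.3%) to be missing from the per-protocol set.

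**The case against.** Per-protocol as the primary set is a recognised convention for non-inferiority, because crossover and non-delivery can pull an intention-to-treat difference towards zero. This stands. The criticism is not that a per-protocol analysis is used, but that it can decide the question without the randomised comparison beside it.

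A reader might infer that intention-to-treat is ruled out for onlay versus sublay. The text does not support that. It says primary, not only, and the general intention-to-treat rule and the statement on withdrawn patients leave room for a supportive analysis in a fuller document. For the same reason, nobody can say from the article that the per-protocol set drops patients with infected or removed meshes. Its definition may sit in the full protocol or SAP, and its absence here is not a fault.

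A reader might also infer that the power claim is wrong, or that only five exclusions per arm are affordable (164 − 159). That does not follow. The figure of 164 is the requirement for the 90%-power comparison with group A, not a non-inferiority sample size. Reaching five assumes that all 16 patients of the dropout allowance (180 − 164) are lost and that none of them overlaps with the per-protocol exclusions. Counted from enrolment, a single analysis can lose 180 − 159 = 21 per arm (11.7%) before power falls below 80%. If the 2-year probability is estimated by Kaplan-Meier, censored patients would still contribute some information.

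Finally, unequal exclusion between the arms is plausible but not documented. Randomising just before closure removes earlier intra-operative events as a cause.

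**Conclusion.** The point holds as a weakness in a stated decision rule. The article gives the non-inferiority conclusion to the per-protocol set, confines its named intention-to-treat analysis to the comparisons with the suture group, and requires no agreement between sets. The conclusion can therefore rest on a post-randomisation subset while the comparison of all randomised patients fails.

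The size of the bias cannot be estimated from the document. The illustration shows only that selective loss of a few per cent of one arm is enough to reverse the result. It rests on assumed counts and on the excluded patients all having a hernia, which is an extreme case.

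The power statement needs no correction for a single analysis. It would need restating only if both sets must pass. The figure of about 165 per arm then assumes 10% hernia in both arms, a nested per-protocol set and the normal approximation.

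**What to change.** 1. Claim non-inferiority of onlay only if the upper one-sided 98.3% limit of the 2-year hernia difference, onlay minus sublay, is below 10 points in both the intention-to-treat and the per-protocol set.
2. Name the techniques in the rule rather than the letters, and reconcile the letters in the Statistical analysis section with those in the Intervention section. With the letters swapped, a rule written as B minus C could be read in the wrong direction.
3. State that patients are not excluded from either analysis set because of post-randomisation outcomes such as infection, mesh removal or re-operation.
4. Keep the power of more than 80% as the figure for one analysis. Add that 80% joint power needs about 165 per-protocol patients per arm out of 180 randomised, with the assumptions stated. Do not give 159 per arm as sufficient, since joint power there is 78.4%.

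The cost is a change of wording, one repeated analysis and a slightly lower chance of claiming non-inferiority. No extra patients or data are needed, provided per-protocol losses stay within about 15 per arm.
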